#### Statistics: Analyzes population and missing data

The analysis will be based on the intention-to-treat principle, including all randomized participants in the analysis, regardless of their compliance with the intervention protocol. Missing data will be addressed using appropriate imputation methods, such as multiple imputations or the last observation carried forward. Sensitivity analyses will be conducted to evaluate the impact of different imputation methods on the results. The analysis population will be clearly defined, and any deviations from the intention-to-treat principle will be reported and justified.

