### Intervention group (Exercise + POBTE)

Patients assigned to the intervention group will be instructed by a physiotherapist in the performance of the TE sessions according to their functional capacity, with reference to their HRmax [40]. They will be prescribed the reference intensity measures for the expected increase in training time indications on potential risks and references for the interruption of the exercise in their case. The duration of the exercise program will be 4 weeks, with 3 sessions lasting a maximum of 45 minutes per session. On alternate days, twice a week, the patient will receive *Pain Oriented Biobehavioral Therapeutic Education (POBTE)* sessions, focusing on the specific parameters described below. The duration of the sessions will be a maximum of 45 minutes each day [41], and the education program will be spread across 8 sessions over 4 weeks. The intervention group will be instructed to refrain from discussing treatment details with participants assigned to the control group until the end of the treatment and follow-up periods.

The main learning areas that to be addressed and the biobehavioral interventions proposed are summarized in Fig 1, and the conceptual framework of the POBTE intervention is explained in detail in Fig 2 and S1 File. The specific cognitive components of the intervention are listed in the general intervention checklist, following the TiDier checklist (see S1 Checklist) and the exercise intervention is presented in S2 Checklist with the CERT checklist, while the Therapeutic Educational Intervention is presented in S3 Checklist with the GREET checklist.

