#### Others

*Pressure Pain Thresholds (PPT)*. Pressure pain thresholds will be assessed through a pressure algometer. The algometer will be applied to different points in the body (elbow and knee) and participants will be asked to indicate the point at which pressure changes to pain. The pressure will be gradually increased at approximately 1 kg/s until the participant indicates feeling pain. The threshold pressure at which the sensation changes from pressure to pain will be recorded in kilograms (kg) and used as an indicator of PPT. Higher PPT values indicate higher pain thresholds. The validity and reliability of using a pressure algometer to measure PPT have been established [53].

*Height and weight*. Both these variables will be determined by patient estimation, with no exploration of them in the measurement process.

*Sociodemographic*. This comprises Age, Marital status (Single, Married, Divorced, Widowed), Employment status (Active, Unemployed, Retired, Temporary disability, Student, Homemaker, Other), Educational level (none, primary, secondary, university), and Gender.

*Exercise*. Among the exercise variables, the parameters described below will be considered:

*Blood pressure and respiratory rate*. Measured with the Anura application, which has demonstrated reliability with a conventional blood pressure measurement of 98% [54].

*Saturation and HR* are Measured with an Oxylink finger pulse oximeter.

All the outcome measurements will be assessed in a random order at baseline, at the halfway point of the treatment, post-intervention, and one- and eight-months post-intervention (Figs 3–5).

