#### Sample size

The determination of the sample size used a t-test for independent means, calculated using G*Power software (Universität Düsseldorf, Germany). The significance level was set at 0.05, and a power of 90% was targeted. The effect size, assessed by Cohen’s d, was predicted based on a mean difference of 2 points in the Visual Analog Scale (VAS), as it is commonly considered the minimum clinically relevant change in many chronic pain conditions [55], and the pooled standard deviation (SD_pooled). This was derived from the standard deviations of the intervention and control groups in a preliminary study, which were 1.29 and 2.61, respectively.

In recognition of the potential underestimation of standard deviations in the pilot study, the original SD values were adjusted using the Upper Confidence Limit (UCL) method, as described by Whitehead et al. [56], based on Browne’s [57] approach. This adjustment, accounting for a 95% confidence level, yielded an SD of 3.227 using the formula [56, 57]: s_UCL^2 = [k/(X_(1-X,k)^2)] s^2.

Consequently, the effect size (d) was calculated as 0.619195 (derived from 2/3.23). With a 1:1 allocation ratio between groups, G*Power [58] indicated a requisite minimum of 56 subjects per group to detect a 2-point difference in VAS with 90% power. Considering a 15% dropout rate, the final sample size was set at 66 subjects per group, totaling 132 subjects for the study to maintain the desired statistical power.

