#### Statistics: Outcome

Data analysis will be conducted using the statistical software SPSS version 25.0 (SPSS Inc., Chicago, IL, USA). A descriptive analysis of the demographic characteristics and pain intensity of the sample size will be performed, presenting continuous variables as mean ± standard deviation (SD) and 95% confidence interval (CI), while categorical variables will be presented as number (n) and percentage (relative frequency, %). In instances where quantitative variables follow a non-normal distribution, they will be described using the median and interquartile range.

For the comparison between groups, parametric tests based on the central limit theorem will be chosen, since the sample size of both groups will be greater than 30 [56]. A mixed-model Analysis of Covariance (ANCOVA) will be used including baseline as the covariate, to obtain between-group adjusted mean differences at each follow-up point, controlling for type I error rate using Bonferroni’s correction. The chi-square test will be used for nominal variables. If the criteria for parametric testing cannot be met, robust methods will be applied [57]. A p-value < 0.05 will be accepted as statistically significant.

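### Last observation carried forward is named as an appropriate missing-data method and not confined to sensitivity analysis, which could bias the 8-month pain comparison

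*Protocol article*

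**What the plan says.** The section of the protocol article on analysis populations and missing data commits to intention to treat, "including all randomized participants in the analysis, regardless of their compliance with the intervention protocol". It then says: "Missing data will be addressed using appropriate imputation methods, such as multiple imputations or the last observation carried forward". The next sentence adds: "Sensitivity analyses will be conducted to evaluate the impact of different imputation methods on the results". Neither method is named as primary, and LOCF is not restricted to a supporting role.

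Four other places bear on this:

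- Statistics: Outcome gives the main model: "A mixed-model Analysis of Covariance (ANCOVA) will be used including baseline as the covariate, to obtain between-group adjusted mean differences at each follow-up point".
- The end of the Outcomes section sets the visits: "at baseline, at the halfway point of the treatment, post-intervention, and one- and eight-months post-intervention".
- The intervention section gives the treatment period: "The duration of the exercise program will be 4 weeks". The control section gives the same period.
- The sample size section expects some loss: "Considering a 15% dropout rate, the final sample size was set at 66 subjects per group".

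**The concern.** LOCF assumes that a patient's pain stays at its last recorded value. That is hard to defend here. The primary outcome is pain at the moment of measurement, treatment stops after 4 weeks, and the final comparison comes 8 months after treatment ends. A patient lost after the programme would enter the 8-month comparison with an end-of-treatment or 1-month score. LOCF also enters that score in the analysis as if it had been observed at 8 months.

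The 8-month estimate carries any conclusion on durability, and the plan reports an adjusted difference at that visit. If LOCF were the primary method, that estimate could reflect an earlier treatment effect. Calling LOCF appropriate is a choice of method that this document states. It is not a detail left to a separate analysis plan.

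**Working it through.** **Inputs from the article.** Difference 2 points, SD 3.23, alpha 0.05, power 90%, 56 per group before and 66 after 15% dropout (Sample size); 4-week programme; visits at mid-treatment, post-intervention, 1 month and 8 months.

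**Assumptions not in the article.** Correlation between visits of 0.3 to 0.7; 15% of 8-month scores missing completely at random in each arm; dropouts last seen post-intervention; the pain courses listed in step 3.

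**1. The plan's own figure.** d = 2/3.23 = 0.6192. A two-sided two-sample t-test at 0.05 has power 0.896 with 55 per group and 0.901 with 56. Then 56/0.85 = 65.9, so 66 per group and 132 in total. The stated sample size reproduces.

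**2. Scores at risk.** 0.15 × 66 = 9.9, so about 10 per arm.

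**3. Expected LOCF difference.** With an equal missing fraction m in both arms, the expected LOCF difference is (1 − m) × (true 8-month benefit) + m × (benefit at the last visit seen). With m = 0.15:

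- 2 points early, 0 at 8 months: 0.85 × 0 + 0.15 × 2 = 0.30 (truth 0).
- 2 early, 1 at 8 months: 0.85 × 1 + 0.15 × 2 = 1.15 (truth 1).
- 2 early, 2 at 8 months: 0.85 × 2 + 0.15 × 2 = 2.00 (no bias).
- 1 early, 2 at 8 months: 0.85 × 2 + 0.15 × 1 = 1.85 (truth 2, so conservative).
- Both arms relapse by 3 points with equal dropout: bias 0.
- Both arms relapse by 3 points, with 20% dropout in one arm and 10% in the other: 3 × (0.20 − 0.10) = 0.30 points (simulated: about 0.27). The arm that loses more patients looks better.

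**4. Precision and type I error.** Simulation of the first course (truth 0 at 8 months), 66 per arm, 8-month ANCOVA on baseline, 1,500 trials per row. Multiple imputation (MI) used 20 imputations from arm, baseline and post-intervention score.

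| Correlation | LOCF false benefit | SE, complete data | SE, LOCF | SE, MI | LOCF SE below MI | Type I, LOCF | Type I, MI |
|---|---|---|---|---|---|---|---|
| 0.3 | 0.27 | 0.536 | 0.544 | 0.585 | 7.0% | 6.9% | 4.6% |
| 0.5 | 0.31 | 0.489 | 0.496 | 0.531 | 6.6% | 8.7% | 4.7% |
| 0.7 | 0.30 | 0.403 | 0.412 | 0.435 | 5.3% | 11.9% | 4.9% |

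Confidence-interval coverage under LOCF was 93.1%, 91.3% and 88.1%, against about 95% for MI. A rejection rate near 9% carries a simulation error of √(0.09 × 0.91/1500) = 0.7 percentage points.

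Hand check of the middle row: 0.30/0.496 = 0.605 standard errors. P(Z > 1.98 − 0.605) + P(Z < −1.98 − 0.605) = 0.085 + 0.005 = 0.09, in line with 8.7%.

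**5. Limit on the standard-error point.** At correlation 0.5 the LOCF standard error (0.496) matches the sampling SD of the LOCF estimator (0.493). It is too small only as a statement of what the observed data say about the 8-month effect. When both arms relapse by 3 points with equal dropout, the spread grows and the gap nearly closes: 0.522 against 0.529 for MI, or 1.3%. In the fading-benefit case, bias is the larger harm.

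**The case against.** The article names multiple imputation first, offers both methods as examples, and plans to compare imputation methods, so a result driven by LOCF should become visible. Data analysts are to be blinded. Details such as delta shifts or covariance structure can fairly wait for an analysis plan. The size of the bias rests on a pain course and a dropout pattern that the article does not give. Patients lost before any post-baseline visit would carry baseline pain forward, which pulls the difference towards zero. Even in the adverse case, 0.3 points is 15% of the 2-point target and about 0.6 of a standard error.

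Most of this stands, and it rules out several stronger readings that a reader might infer:

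- That LOCF would necessarily inflate the 8-month benefit. The direction depends on the pain course and on who drops out, and LOCF may not be the method used.
- That the standard error would be 8% too small, from √(56/66) = 0.921. That compares LOCF with complete cases. Against multiple imputation the gap is 5–7%, and it can nearly vanish.
- That the planned mixed model already makes imputation unnecessary. The article does not name likelihood estimation, and a mixed-model ANCOVA can also mean a repeated-measures analysis that drops incomplete cases.
- That the sensitivity analyses leave the missing-data assumption untouched. LOCF and multiple imputation assume different things, so comparing them varies the assumption, though crudely.
- That the method would be picked once results are known. No text says so.

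What the objection does not remove is that LOCF is called appropriate without restriction. A comparison between methods also does not say which result counts when they disagree.

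**Conclusion.** The point holds in a conditional form. The article accepts LOCF level with multiple imputation for the intention-to-treat analysis, in a trial whose last visit falls 8 months after a 4-week programme. About 10 of 66 8-month scores per arm could be affected at 15% dropout.

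If a 2-point early benefit is fully lost by 8 months and dropouts were last seen post-intervention, the false benefit is about 0.3 points, type I error is about 7–12%, and the standard error is 5–7% below that of multiple imputation. If the benefit persists, or both arms relapse and drop out equally, the bias is near zero. If the benefit grows, LOCF is conservative. A method whose error changes direction with an unknown pain course should not be open as the primary method. This should be corrected before analysis. It does not affect the sample size.

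**What to change.** - Remove LOCF from the eligible primary methods, or keep it only as a labelled sensitivity analysis.
- Name one primary approach that is valid under missing at random. Either specify the planned mixed model as likelihood-based on all observed visits, or specify multiple imputation.
- Add a sensitivity analysis for departures from missing at random: multiple imputation with a delta adjustment, or control-based imputation.

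The cost is a change of wording and a small amount of extra programming. Visits, treatment and sample size stay as they are.

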#### Data monitoring: Formal committee

This small-scale, low-risk intervention trial does not require a Data Monitoring Committee (DMC). Instead, the study investigators will take on the responsibility of monitoring trial data. The primary investigator will regularly review study data to ensure protocol adherence and to maintain the safety and well-being of participants. In the event of significant safety concerns or other issues, the primary investigator will collaborate with the study team and, if deemed necessary, seek guidance from an independent expert to determine the best course of action. Any concerns or protocol deviations will be promptly reported to the relevant regulatory authorities.

#### Data monitoring: Interim analysis

Although data and blood samples will be collected for 15 days during the intervention period, no interim analyses are planned for this trial. Nevertheless, it could be of interest to check potential changes in BDNF levels, which serve as a biomarker of brain plasticity, in relation to the learning curve [60] observed in patients. It is expected that the learning process during the intervention will lead to significant changes in BDNF levels.

#### Harms

The research team will vigilantly monitor participants for adverse events related to the intervention or trial conduct. Solicited events will be assessed during follow-up visits, while spontaneously reported events will be identified during unscheduled interactions.

Adverse events will be documented, and the principal investigator will conduct a thorough review to determine whether they require reporting to the ethics committee and regulatory authorities. Unintended effects coming from the trial interventions or conduct will also be closely monitored and appropriately managed. All events will be reported in the trial report, publication, and to the ethical committee.

#### Research ethics approval

To get approval for our study from a research ethics committee (REC), we developed a detailed protocol, submitted the requisite documentation, addressed any queries or concerns raised by the REC, obtained REC approval, and will ensure ongoing compliance. Additionally, we have established plans to communicate important protocol modifications to investigators, the REC, trial participants, trial registries, journals, and regulators.

#### Consent or assent

Informed consent or assent will be obtained from potential trial participants or authorized surrogates by trained research staff. The consent process will involve the use of written informed consent documents, which will be provided to the potential participants or their authorized surrogates in advance of the trial. These documents will include a detailed description of the study, the associated risks and benefits of participation, as well as the rights and responsibilities of the participants. Research staff will also be readily available to answer any questions or concerns that may arise during the consent process.

#### Consent or assent: Ancillary studies

We have included provisions in the informed consent form to cover potential ancillary studies involving participant data and biological specimens. The form clearly states that data and specimens may be used for future research with ethical approval, and participants have the right to withdraw their consent at any time. This approach ensures that participants are fully informed and that their rights and privacy are protected.

#### Confidentiality

Throughout the trial, we will protect participants’ personal information. During the screening process, only essential information will be collected, and any unused data will be destroyed. Personal information will be kept secure and restricted to authorized members of the study team, identified solely by participant ID numbers. Upon completion of the trial, identifying information will be removed, and data will be securely stored for a specified period. Participants will be informed of our confidentiality policies during the informed consent process.

#### Data access

No datasets were generated or analysed during the current study. All relevant data from the RCT will be made available upon study completion.

#### Ancillary and post-trial care

The study team will develop a plan to provide ancillary or post-trial care for any harm experienced by participants during a clinical trial. Participants will be informed about these plans during the informed consent process and will work with regulatory authorities and review boards to ensure the implementation of appropriate provisions.

#### Dissemination policy: Trial results

We will communicate the trial results to participants, healthcare professionals, and the public. Results will be published in a peer-reviewed journal, presented at conferences, and reported in publicly accessible databases. Lay summaries will be provided to participants, and healthcare professionals will receive information. We will publish results regardless of the outcome, share the protocol, dataset, and statistical analysis, and adhere to responsible research guidelines. Our communication will be clear, timely, and accurate, with integrity and transparency.

#### Dissemination policy: Authorship

Authorship eligibility guidelines will follow international standards [61]. The contributions of eligible individuals will be clearly stated in publications, and professional writers will only be acknowledged if they meet the authorship eligibility guidelines.

#### Dissemination policy: Reproducible research

After the study, we will share the complete protocol, de-identified participant-level dataset, and statistical analysis, encouraging transparency and enabling further research. To enhance the accessibility and reproducibility of study findings, we will provide technical support and educational resources.

## Discussion

The current randomized controlled trial (RCT) seeks to examine the impact of a specific therapeutic education program, combined with exercise, on BDNF levels and perceived pain intensity among individuals suffering from chronic musculoskeletal pain. This article not only seeks to offer a more rigorous approach to therapeutic education from a biobehavioral perspective but also assesses the outcomes of an intervention that encompasses both the cognitive aspects and pain-related plasticity biomarkers, such as BDNF. Consequently, it represents a valuable contribution to low-cost, non-pharmacological treatments in physiotherapy. Although the study design and methods have been meticulously planned, several practical and operational considerations need to be addressed.

One potential limitation of our study pertains to the heterogeneity of chronic pain. Despite having well-defined inclusion criteria, it is important to acknowledge that chronic pain is a complex and multifactorial condition [62–64]. While we have not imposed restrictions on the specific site of pain in our selection criteria, a stance supported by evidence suggesting that chronic pain is centrally mediated rather than solely dependent on the location of the injury [65–68], it is evident that various individual factors influence the pain experience in each patient [69–71]. These factors may impact the results obtained. To address this limitation, in addition to the inclusion criteria, we will consider conducting subgroup analysis if deemed necessary and feasible. This analysis will enable us to examine possible clusters of patients with similar characteristics, thereby enhancing our understanding of differences and treatment responses within our sample. It is also important to highlight that, regarding the proposed statistical analysis, it is assumed that categorical variables with more than five categories can be considered as continuous variables. This approach has been extensively considered in scientific literature and previously validated [72]. However, this could influence the final choice of the analysis method selected for the study.

Another concern is the potential confounding effects of medications and other interventions that participants might be undergoing. To address this issue, participants will be strongly advised to maintain their regular medication regimen (if applicable) but will not be permitted to initiate any new treatments during the program and follow-up period. This measure is implemented to minimize potential confounding factors and ensure the integrity of the study results. The study team will diligently screen and monitor participants to ensure compliance with this requirement. Additionally, the statistical analysis will consider adjusting for any emerging confounding variables.

Finally, it is important to note that the measurement of BDNF levels can pose challenges due to the inherent variability in sample collection, storage, and analysis. In this study, BDNF levels will be specifically measured in plasma samples, as they have been found to be more stable during analysis compared to serum samples [73]. To ensure precise and reliable results, the study team will adhere to rigorous protocols for plasma sample collection, processing, and storage. The analysis will be conducted using standardized ELISA kits, with regular calibration and quality control checks implemented to minimize potential sources of variation. These measures are crucial for ensuring the accuracy and validity of the BDNF measurements and upholding the integrity and reliability of the study’s findings.

In conclusion, this randomized controlled trial serves as a significant milestone in two important aspects. Firstly, it contributes to the development of a more structured and rigorous therapeutic education model for individuals with chronic musculoskeletal pain by implementing validated checklists and protocols [31, 32]. This standardized approach ensures the delivery of effective interventions tailored to the specific needs of these patients.

Secondly, the study investigates the changes occurring at the central nervous system level by measuring biomarkers such as BDNF. This provides valuable insights into the underlying mechanisms of chronic pain and the impact of non-pharmacological interventions on brain plasticity. By elucidating the relationship between therapeutic education, BDNF levels, and pain outcomes, this research can pave the way for novel and targeted strategies to enhance treatment efficacy and improve the quality of life for individuals suffering from chronic pain.
